### Details of ethics approval

The study design, protocols, procedures and IC were approved by the Medical Ethics Committees of all participating hospitals: the VU University Medical Center (date 22-10-2009, number 2009/218), the Amstelland Hospital (12-02-2010, number 10-54), the Flevo Hospital (date 10-12-2009, number FZ09/35), the Kennemer Gasthuis (03-03-2010, number 2010.02), the Onze Lieve Vrouwe Gasthuis (date 21-01-2010, number 09.067), the Sint Lucas Andreas Hospital (03-11-2009, number 09/114) and the Spaarne Hospital (20-01-2010, number 561.09).

## Discussion

This paper describes a RCT to study the effect of a multidisciplinary care program on recovery and full sustainable return to work of women who underwent a hysterectomy and/or a laparoscopic adnexal surgery on benign indication. Since work participation contributes to well-being and recovery of illness, the program particularly pays attention to stimulate patients in gradually resuming normal activities including RTW [13,55]. During the first step of the multidisciplinary care program, all patients get access to the e-health intervention, which primarily aims to empower patients' behavioural determinants and supports adequate beliefs regarding recovery and RTW in patients with an uncomplicated postoperative course [18]. These are prognostic factors for recovery and RTW and account for the personal determinants in the ICF model. Secondary, the e-health intervention provides tools through which environment (e.g. family, employer), clinical condition, participation and resuming of activities may be influenced. The second step of the care program is only offered when sick leave exceeds ten weeks and thus to patients with a complicated recovery and RTW. The goal of this step is to prevent work disability. It contains additional integrated care management by a multidisciplinary team consisting of a clinical occupational physician, gynaecologist and OT and includes a workplace intervention. This step mainly focuses on reducing barriers for RTW by improving communication between different care providers, OP, employer and patient.

### Strengths and limitations

The implementation of this study in six general (teaching) and a University hospital is a good reflection of the Dutch health care situation. In addition, the selection bias of patients will be restricted through the proactive way of inviting all patients on the waiting lists to participate in the RCT. Therefore, selection will take place only based on clearly defined in- and exclusion criteria. A third strength is the blinding of the patients, which will minimize the Hawthorne and placebo effect [56]. Furthermore, the primary outcome measure in this study is full sustainable RTW, which takes into account recurrences of sick leave within four weeks after RTW and therefore reduces underestimation of work-loss days [57]. Another strength regarding the outcome measures is the evaluation of patients' health and recovery through clinical, participatory and activity outcome measures. By doing so, the influence of the care program on the different aspects of human functioning and state of health according to the ICF model, will be evaluated [14]. All patients receive their own research code according to which all data were stored in the databases. This ensures blinded analysis of the data by the researchers. Finally, this is the first study to extensively evaluate consensus-based guidelines with detailed convalescence recommendations regarding return to normal and work activities after gynaecological surgery [18,58]. The guidelines represent a consensus opinion of expert-based knowledge between gynaecologists, GPs and OPs and this study will show whether these recommendations reflect realistic recovery times for gynaecological patients and will bring about a quicker recovery without an increase in complications compared with usual care.

The main limitation of this study is that contamination between the intervention and control group cannot completely be prevented, because the randomization will be performed on patient level. With regard to the health care providers, it is impossible to blind them for the intervention allocation, because the allocation determines the kind of convalescence recommendations that should be given to the patient. Therefore, it is important for them to follow and distinguish consequently the protocol belonging to the intervention versus the control group. Contamination may occur when care providers use acquired insights received through the convalescence recommendations for the intervention group to adapt their usual care and convalescence recommendations given to the control group. To minimize this effect, we will only proactively work on the familiarity of the protocols among the health care providers and not on the detailed contents of the convalescence recommendations for the patients in the intervention group. The patients' gynaecologists will only receive a summary of the guideline by means of their patients' record, in order to pass it on to the patient at discharge from the hospital. GPs and OPs will only receive the guideline when the patient hands over her tailored convalescence recommendations or work reintegration plan to them. A learning curve of the health care providers to flawlessly execute the protocol in the intervention group may be expected. This implementation curve may result in less effect of the intervention during the beginning of the study, which should receive attention during the analysis of the results. To accelerate the implementation of the protocol, pocket maps with the description of the intervention will be distributed, teaching meetings with the health care providers about the protocol will be organized and the protocol will be added to the medical file of the patient. Although therapists and researchers cannot be blinded for the allocated treatment of the patient, they will not be involved in measuring the outcomes, since all outcome measures are self-reported and the questionnaires will be sent by email or post to the patients. Therefore, it is unlikely that the way patients complete the questionnaires, will be influenced by the researcher and care providers. Moreover, the therapists of the multidisciplinary team (RTW-coordinator, OT, and other care providers), will not be involved in the assessment of the outcomes. With concern to contamination between patients of the intervention and control group, a chance meeting cannot be excluded. According to the protocol, patients from different groups should not be placed in the same hospital room, but it cannot be prevented that patients will meet outside the room. Another limitation of this study is the fact that the integrated care management and the workplace intervention will be carried out by one clinical occupational physician and OT, which might affect the execution of the intervention. However, both will work according to a detailed standardized protocol in order to minimize their personal influence on performance of the intervention as much as possible. Compliance to e-health interventions is sometimes low. We tried to minimize the risk of low compliance as much as possible by spending extra effort and time on involving the stakeholders (end-users) in the development of this intervention and adapting it to their specific needs by use of the intervention mapping protocol [22]. Finally, although the participating hospitals reflect the proportion of (non) university hospitals in the Netherlands, they are all located in the urban agglomeration in the Western part of the Netherlands, which might be of influence on the educational level of the patient population. Because research has shown that both living in the city as well as higher educational level are associated with more frequent use of the internet for health or illness matters, it should be determined whether the educational level and internet use of the participating patients reflects that of the general Dutch population, before the results of this study can be interpreted as representative of all gynaecological patients in the Netherlands [59].

### Policy implications

Yearly more than 17.500 women receive a hysterectomy or laparoscopic adnexal surgery on benign indication in the Netherlands [19]. These large numbers of surgeries have a great impact on absenteeism since it is expected that approximately 67 percent of women aged between 25 and 65 years have paid work [60]. Therefore, if this multidisciplinary care program reduces medical consultation by providing patients with tailored, detailed and unambiguous convalescence recommendations, improves communication between care providers and stimulates patients in a faster sustainable RTW, this relatively cheap intervention may potentially decrease the sick leave costs of gynaecological patients in the Netherlands.

If the multidisciplinary guidelines evaluated in this study will bring about a quicker recovery without an increase in complications, they will be implemented broadly in the Netherlands in collaboration with the participating medical board of gynaecologists, OPs and GPs. After implementation, the expectation is that the guidelines will result in more unambiguous detailed convalescence recommendations given by gynaecologists, GPs and OPs, through which patients will be better informed about when it is medically safe to resume daily and work activities after gynaecological surgery and give them the possibility to arrange (workplace) adaptations if necessary. Furthermore, the unambiguous recommendations will likely enhance the compliance to advice given by medical specialists and stimulate the patient to resume activities with increasing gradations of strain, which will presumably bring about a quicker recovery without an increase of complications [61,62]. Therefore, the guidelines may potentially prevent work disability, increase quality of life (QoL) and increase patient satisfaction with care.

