### Sample size

Power calculation was performed on the primary outcome (all kind of surgeries together). To achieve a power (1-β) of 80%, with a significance level (α) of 5% and considering a HR of 1.5 in favour of the intervention group, approximately 191 patients will be needed. Anticipating a 10% drop out rate, in total a sample size of at least 212 patients will be aimed for. To recruit this number of patients, the study will anticipate on a ten-month inclusion period.

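### Broad roll-out is tied to finding no increase in complications, but a trial sized only on return to work cannot exclude a sizeable increase

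*Protocol article*

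**What the plan says.** Three places in the protocol article matter.

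- **Discussion, Policy implications.** Implementation is conditional: if the guidelines "will bring about a quicker recovery without an increase in complications, they will be implemented broadly in the Netherlands". It is to be done together with the participating professional boards.
- **Discussion, Strengths and limitations.** Among the strengths, the article says the study will show whether the recommendations reflect realistic recovery times and "will bring about a quicker recovery without an increase in complications compared with usual care". This poses an open question. It does not predict the answer, but it does claim that the trial can give one.
- **Methods/Design, Sample size.** "Power calculation was performed on the primary outcome (all kind of surgeries together"). The calculation is for 80% power at a 5% significance level, "considering a HR of 1.5 in favour of the intervention group"; the result is that "approximately 191 patients will be needed". It continues: "Anticipating a 10% drop out rate, in total a sample size of at least 212 patients will be aimed for".

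Post-operative complications are secondary outcome 9 and are self-reported. Table 3 schedules them for both arms at 6, 12 and 26 weeks. The intervention arm also reports them through the website, more often. The Data analysis section describes methods for return to work only. The long discussion of limitations covers contamination, provider effects, compliance and generalisability, but not precision for complications.

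**The concern.** The roll-out condition has two halves, quicker recovery and no increase in complications. The sample size supports the first half. Nothing in the article shows that it supports the second, and the statement that the study will show whether both hold suggests that it does.

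The program encourages women to resume activities and work, so more complications are the obvious possible harm. The article itself says the extra website reporting serves partly to register side effects. If complications rose moderately, a trial of this size could easily fail to reveal it, and the roll-out statement could be taken as satisfied. The policy covers procedures that number more than 17,500 a year in the Netherlands.

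**Working it through.** **The plan's own figure.** Schoenfeld's formula with HR 1.5, two-sided 5%, 80% power and 1:1 allocation gives 4 × (1.960 + 0.842)² / (ln 1.5)² = 191, as stated. The article does not give the sidedness; the one-sided version gives 151. Dividing by 0.9 gives 212.2, against the stated 212. So 191 is the return-to-work requirement, and complications played no part in it.

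**Inputs for complications.** Analysed per arm: 191/2, taken as n = 95. The control complication rate p is not in the article, so 5% to 40% is assumed.

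**What equal observed rates would leave open.**

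- Risk difference, upper 95% limit: 1.96 × √(2p(1−p)/n). At p = 0.10: 1.96 × √(0.18/95) = 1.96 × 0.0435 = 8.5 points.
- Risk ratio, upper 95% limit: exp(1.96 × √(2(1−p)/(np))). At p = 0.10: exp(1.96 × 0.435) = 2.35.

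**Power (two-sided 5%).** Φ[(d − 1.96·se₀)/se₁], where d is the true difference, se₀ the pooled and se₁ the unpooled standard error. For 10% against 15%: (0.05 − 1.96 × 0.0480)/0.0479 = −0.92, so power is 18%.

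| Assumed control rate | Upper risk difference | Upper risk ratio | Power, true 50% increase | Power, true doubling |
|---|---|---|---|---|
| 5% | +6.2 points | 3.45 | 11% | 26% |
| 10% | +8.5 | 2.35 | 18% | 49% |
| 15% | +10.2 | 1.97 | 26% | 70% |
| 20% | +11.4 | 1.77 | 36% | 86% |
| 30% | +13.0 | 1.54 | 57% | 99% |
| 40% | +13.9 | 1.42 | 79% | >99% |

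The two scales do not give the same upper rate. At 10%, the risk-difference limit corresponds to 18.5%, or 1.85 times control, against 2.35 on the ratio scale. The relative statements below use the ratio scale. With 106 per arm (no dropout) the upper risk ratio is 2.24 at 10% and 1.71 at 20%, so the picture hardly changes.

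**Two ways the condition might be read.** The article fixes neither.

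| Reading of no increase | True change | Chance of passing at control 5% / 10% / 20% |
|---|---|---|
| Test not significant (1 − power) | +50% | 89% / 82% / 64% |
| Test not significant (1 − power) | doubling | 74% / 51% / 14% |
| Observed count not higher (exact binomial) | +50% | 29% / 17% / 6% |
| Observed count not higher (exact binomial) | doubling | 12% / 3% / 0.1% |

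**Would a margin held elsewhere cure this?** For one-sided 2.5%, 80% power and equal true rates, n per arm = 2p(1−p)(1.960 + 0.842)²/margin². Purely to illustrate, a 10-point margin needs 75 per arm at 5%, 142 at 10% and 252 at 20%. A 5-point margin needs 299, 566 and 1005. About 95 per arm is enough only in the first case, where 10 points means a tripling from 5% to 15%.

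**The case against.** The strongest reply has four parts.

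- **This is a Discussion paragraph in a condensed article.** The roll-out sentence is a statement of intent involving professional boards, not a hypothesis test. Sizing a trial on its primary outcome is normal, and a margin or analysis for a secondary outcome may sit in a document not shown. This stands as far as it goes: a missing margin is not the finding. The finding is the capability that the article claims, and a margin elsewhere would not supply the precision unless it were wide relative to the control rate.
- **A reader might infer that a non-significant result will be taken as proof of safety.** The article does not say so; it states no test or rule for complications. The inference should not be attributed to it.
- **A reader might infer that a doubling of complications would often slip through.** That depends on a control rate the article does not give and on how the condition is read. If it means the observed rate is not higher, a doubling passes only about 12%, 3% and 0.1% of the time at 5%, 10% and 20%. At control rates of 30% to 40%, equal observed rates would exclude a doubling.
- **A reader might infer that the plan promises no increase.** It says the study will show whether there is one.

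These points narrow the claim. They do not remove the mismatch between the roll-out condition and the trial's precision.

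**Conclusion.** The concern holds in a limited form: the article credits the trial with settling a safety condition for which its sample size gives too little precision.

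With about 95 per arm and equal observed rates, increases of about 6 to 14 points remain compatible with the data over assumed control rates of 5% to 40%. In relative terms, a doubling cannot be excluded at rates up to about 10%, nor a near doubling up to about 15–20%. Even at 30–40% an increase of roughly 40–55% cannot be excluded. A true 50% increase would be detected only 11%, 18% and 36% of the time at 5%, 10% and 20%.

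Neither a non-significant test nor an observed rate that is not higher would establish that complications do not increase. The sizes rest on the assumed rates, normal approximations for the limits and power, and 95 analysed per arm. The return-to-work analysis is unaffected.

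**What to change.** 1. In Strengths and limitations and in Policy implications, say that the trial estimates the between-arm difference in post-operative complications. Use only the 6-, 12- and 26-week questionnaires common to both arms, and report the risk difference with its 95% confidence interval.
2. State that a non-significant or null observed difference will not by itself be read as no increase.
3. Base the implementation statement on the upper confidence limit, judged against a tolerable increase that the sponsor and the medical boards set before analysis. If the limit exceeds it, report safety as inconclusive. The size of that increase is theirs to choose; the essential change is to rely on the interval.
4. Add the limited precision for complications to the limitations.

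The cost is wording and one confidence interval, with no extra patients or data. The downside is that the roll-out claim becomes less favourable and may stay open when the trial ends.

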## Abbreviations

BQ: Baseline Questionnaire; GP: General Practitioner; IC: Informed Consent; ICF: International Classification of Functioning; ITT: Intention-To-Treat; OP: Occupational Physician; OT: Occupational Therapist; RCT: Randomized Controlled Trial; RTW: Return To work
